### Sample size considerations

3.6.

AAML1831 will enroll approximately 1,400 subjects over an estimated 5-year accrual period. The integrated cardiac studies are designed to address cardiac-specific aims within a representative subcohort of the study population with the primary emphasis on comparing the cardiotoxicity across arms. The case cohort is constructed to identify predictors of cardiotoxicity will incorporate cases from the entire study population (analyzing those treated on Arms C/D with gilteritinib separately). Estimating an LVSD rate of 8% in the conventional chemotherapy arm (inclusive of dexrazoxane) based on AAML1031 data and 5% in the CPX-351 arm, 33 cases are anticipated within the subcohort plus an additional 33 cases from the non-FLT3 mutant population (i.e., Arm A/B) outside of the subcohort (*n* = 510). Thus, the overall case cohort will consist of 543 patients, including 66 cases (40 for the standard arm, 26 for the CPX-351 arm). An estimated 33% of the 510 patients included in this analysis will be at high risk; thus, expect 84 high-risk and 171 low-risk patients per arm. Assuming an LVEF standard deviation of 10%, there will be 80% power to determine a difference between treatment arms of 6% LVEF for high-risk patients and 4% LVEF for low-risk patients, accounting for correlations between repeated measures by GEE. Assuming a GLS standard deviation of 2.5%, there will be 80% power to determine a difference between treatment arms of 1.2% GLS for high-risk patients and 1% GLS for low-risk patients.

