### Intervention/trial design

3.2.

In this phase 3 COG study, children and adolescents with newly diagnosed AML were randomized 1:1 at enrollment to receive standard daunorubicin and cytarabine-containing induction therapy with dexrazoxane vs. CPX-351. All patients will undergo two induction cycles with either daunorubicin (50 mg/m^2^ on days 1, 3, and 5 of each cycle)/cytarabine or CPX-351 (135 units/m^2^/dose, equal to 60 mg/m^2^/dose of daunorubicin on days 1, 3, and 5 of induction and 115 units/m^2^/dose, equal to 50 mg/m^2^ of daunorubicin on days 1, 3, and 5 of induction 2).

Patients deemed high risk based on disease response or molecular/cytogenetic features will undergo a single intensification cycle followed by HSCT (52). Those with low-risk features will undergo 2–3 intensification cycles depending on their cytomolecular features and response. Subjects with favorable cytomolecular features and minimal residual disease <0.05% at the end of induction 1 are assigned to the lowest-risk arm [low risk 1 (LR1)]. LR1 subjects will receive only two intensification cycles without mitoxantrone. Patients whose AML harbors FLT3 internal tandem duplication or activating mutations will also be offered participation in arms that add the tyrosine kinase inhibitor gilteritinib (Arms C/D). An overview of therapeutic agents included in each induction and intensification cycle is shown in the study schematic (Figure 1). All patients will enter follow-up and continue to submit cardiac AEs, LVEF/LVFS data, and DICOM echocardiographic images for 10 years after completion of protocol therapy unless they are removed from the study due to death, loss of contact, withdrawal of consent, or enrollment on another COG anti-cancer therapeutic trial. The current clinical trial was approved by the Pediatric Central Institutional Review Board (CIRB) and the COG Scientific Council.

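### The 80%-power differences for LVEF and GLS are not reproduced from the stated n and SD, and the GLS pair does not fit 84 and 171 patients per arm

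*Protocol article*

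**What the plan says.** Section 3.6 (Sample size considerations) of the protocol article splits the 510-patient subcohort by risk group: "thus, expect 84 high-risk and 171 low-risk patients per arm". Section 3.2 gives the allocation: "children and adolescents with newly diagnosed AML were randomized 1:1 at enrollment".

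For LVEF the SD is 10%, and the plan claims "80% power to determine a difference between treatment arms of 6% LVEF for high-risk patients and 4% LVEF for low-risk patients", described as "accounting for correlations between repeated measures by GEE". The GLS statement opens: "Assuming a GLS standard deviation of 2.5%, there will be 80% power to determine a difference between treatment arms of 1.2% GLS for high-risk". Its low-risk counterpart is 1%.

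Section 3.5.1 plans the same analysis for both outcomes: GEE on core-lab values from all precycle echocardiograms, end of therapy and 12 months off therapy. The article does not give the significance level, sidedness, within-patient correlation, evaluable share, or the contrast on which the four differences rest.

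**The concern.** Two things stand out. First, each stated difference is larger than a simple comparison with these sample sizes and SDs would need for 80% power. Second, the four figures do not scale together. In SD units they are 0.60 (LVEF) and 0.48 (GLS) for the same high-risk patients, but 0.40 for both outcomes in low-risk patients. Within GLS, doubling the sample from 84 to 171 per arm changes the detectable difference much less than it should.

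These are the article's only power statements for the randomised core-lab comparison of LVEF and GLS. If that comparison shows no difference, readers will use these figures to judge what size of effect the study could have missed, so each should mean what it says.

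**Working it through.** **Inputs.** From section 3.6: n per arm 84 (high-risk) and 171 (low-risk); SD 10 (LVEF) and 2.5 (GLS); power 80%; stated differences 6, 4, 1.2 and 1. From section 3.2: 1:1 allocation. Assumed: two-sided alpha 0.05, normal approximation, no correlation adjustment and no attrition.

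**Step 1: reference calculation.** Detectable difference = (1.960 + 0.842) × SD × sqrt(2/n) = 2.8016 × SD × sqrt(2/n). Power at a stated difference d is Φ(d / (SD × sqrt(2/n)) − 1.960). The variance factor is (stated / reference)², and its range allows for rounding of the stated figure (LVEF to the nearest 1, GLS to the nearest 0.1).

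| | Stated | Reference | Power at stated | n per arm for 80% | Variance factor (range) |
|---|---|---|---|---|---|
| LVEF, high-risk | 6 | 4.32 | 97.3% | 44 (52% of 84) | 1.93 (1.62–2.26) |
| LVEF, low-risk | 4 | 3.03 | 95.9% | 99 (58% of 171) | 1.74 (1.33–2.21) |
| GLS, high-risk | 1.2 | 1.08 | 87.5% | 69 (82% of 84) | 1.23 (1.13–1.34) |
| GLS, low-risk | 1.0 | 0.76 | 95.9% | 99 (58% of 171) | 1.74 (1.57–1.92) |

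None of the stated figures is reproduced. A common variance factor of about 1.62 to 1.92 fits three of them but not high-risk GLS. No single alpha fits either: the two-sided values implied by the four figures are about 0.002, 0.004, 0.023 and 0.004.

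**Step 2: ratio within each outcome.** If SD, alpha, power and method are the same in both risk groups, everything except n cancels:

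high-risk : low-risk = sqrt(171/84) = 1.43, whatever alpha was used.

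- LVEF: 6/4 = 1.50. Rounding allows 5.5/4.5 = 1.22 to 6.5/3.5 = 1.86. This is consistent.
- GLS: 1.2/1.0 = 1.20. Rounding to 0.1 allows 1.15/1.05 = 1.10 to 1.25/0.95 = 1.32. This is not consistent.

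**Step 3: size of the GLS discrepancy.**

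- If 1.2 is right for high-risk, low-risk should be 1.2/1.427 = 0.84. Power at 1.0 would then be Φ(2.8016 × 1.0/0.841 − 1.960) = Φ(1.37), about 91%.
- If 1.0 is right for low-risk, high-risk should be 1.0 × 1.427 = 1.43. Power at 1.2 would then be Φ(2.8016 × 1.2/1.427 − 1.960) = Φ(0.40), about 65%.

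**Step 4: can one unstated input explain the GLS pair?**

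- Attrition: it would have to leave 82% of high-risk but 58% of low-risk patients evaluable.
- Change from baseline, variance factor 2(1 − ρ): ρ would have to be 0.33–0.43 in high-risk and 0.04–0.21 in low-risk patients.
- Number of echocardiograms: section 3.2 gives high-risk patients one intensification cycle before transplant and low-risk patients two to three. For an averaged contrast, extra low-risk measurements would raise the ratio above 1.43. The stated ratio errs the other way.

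**The case against.** The strongest reply is that a single-time-point comparison is not the planned analysis. Section 3.5.1 compares declines by GEE, and for a change from baseline the variance is 2(1 − ρ)SD², which exceeds SD² whenever ρ is below 0.5. Repeated measures therefore need not make the detectable difference smaller. With correlations specific to each outcome (assumed; none is given), one formula comes close to all four figures. LVEF with ρ = 0.10 gives 4.32 × sqrt(1.80) = 5.80 and 3.03 × sqrt(1.80) = 4.06. GLS with ρ = 0.385 gives 1.08 × sqrt(1.23) = 1.20 and 0.757 × sqrt(1.23) = 0.84. An evaluable share of 58% likewise gives 5.68 and 3.98 for LVEF and 0.99 for low-risk GLS. A condensed article may also leave such inputs to the full protocol.

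Much of this stands. A reader might infer that the four figures cannot come from any one method, or that the authors assumed zero within-patient correlation. The documents support neither: LVEF and GLS may have different correlations, and more than one assumption reproduces three of the figures. Missing inputs in a condensed article are not in themselves the fault.

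The reply does not rescue the GLS pair. The outcome-specific account yields 0.84 for low-risk patients, which becomes 1% only if rounded to a whole number next to a figure given to one decimal. The 58% account gives 1.42, not 1.2, for high-risk patients.

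**Conclusion.** The point holds in limited form. The four differences are not reproduced from the stated n and SD at two-sided 5%. The GLS pair is out of proportion to 84 and 171 per arm (1.20 against 1.43), so at least one GLS figure is wrong or too coarsely rounded to carry an 80% power claim. The ratio argument assumes one SD and one method across risk groups; section 3.6 gives one SD and nothing that would separate the groups other than n.

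A reader might go further and conclude that the core-lab comparison is underpowered or that its stated power is wrong throughout. The documents do not support that. On the stated n and SD all four differences have more than 80% power, and the LVEF pair agrees with itself and could reflect an unstated correlation, change contrast or evaluable share. The 65% power for high-risk GLS applies only if the low-risk figure of 1.0% is the correct one.

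This should be fixed, but it is not critical. The cardiac aims are secondary to event-free survival, and no endpoint, test or sample size changes.

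**What to change.** Recompute the four detectable differences for the planned GEE contrast on one basis, and state that basis in section 3.6: alpha and sidedness, the contrast (mean level, change from baseline or a single time point), the within-patient correlation for each outcome, and the evaluable share of echocardiograms. If an input differs by risk group, say so.

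Correct at least the GLS pair, so that both figures follow from 84 and 171 per arm and are given to the same number of decimals. The values 4.3, 3.0, 1.08 and 0.76 are a reference without correlation or attrition, for checking the recalculation; they are not proposed replacements.

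The cost is one recalculation and a wording correction. Patients, procedures and the planned analysis are unaffected.

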## Study status

4.

AAML1831 was initially CIRB approved on 4 March 2020 and activated on 20 July 2020. AAML1831 is currently enrolling subjects with newly diagnosed AML at eligible COG sites. Complete study accrual is anticipated near the end of 2025.

## Discussion

5.

AAML1831 is the largest pediatric oncology trial to prospectively assess, in a randomized fashion, the efficacy of two cardioprotective strategies. Detailed cardiac phenotyping of this large cohort with serial echocardiograms and cardiac biomarkers will allow for robust measure of the cardiovascular impacts of conventional daunorubicin with dexrazoxane as compared to liposomal daunorubicin (CPX-351). While prior COG AML drug trials have relied upon limited site-dependent reporting of cardiac adverse events and site-measured echocardiographic measures, AAML1831 is the first phase 3 pediatric oncology trial to employ rigorous core laboratory echocardiographic image quantitation, a methodology that has become more standard in adult oncology trials. Numerous studies have demonstrated the superiority of core lab interpretations for reducing variability and enhancing the precision of echocardiographic measurements (55–59). Thus, the use of central review in the context of AAML1831 will allow for a more precise and accurate assessment of cardiac outcomes across arms to inform the effects of cardioprotective strategies in the modern treatment era. Central review will also enable a detailed assessment of very comprehensive quantitative echocardiographic measures, including cardiac structure, size, and function, throughout AML therapy and in follow-up to advance the understanding of the trajectory of cardiac remodeling and function with AML therapies and identify early predictors of anthracycline cardiomyopathy where early institution of cardioprotective medications may attenuate subsequent LVEF decline and improve the likelihood of recovery (54, 60, 61).

In addition to primary cardioprotection with dexrazoxane and the use of a liposomal encapsulated anthracycline, AAML1831 employs a rigorous, standardized approach to identifying and managing cardiotoxicity that seeks to balance the potentially competing goals of cardiotoxicity reduction and maximizing anthracycline delivery to optimize both leukemia and cardiovascular outcomes (62, 63). Although challenging, the implementation of a standardized echocardiogram acquisition protocol, comprehensive site echocardiography lab training and regular feedback to optimize the quality of images captured, and the prioritization of LVEF quantitated by the biplane Simpson's method will improve the reliability of cardiotoxicity assessment on which sites are basing the safety of ongoing anthracycline administration. In addition, to maximize the delivery of effective cancer therapy, AAML1831 employs a relatively low threshold for anthracycline dose modification (LVEF < 50%), protocol guidance for a repeat echocardiogram in 1 week to assess for recovery prior to withholding anthracyclines, potential reintroduction of anthracycline therapy in patients with transient LVSD, and recommended cardiology consultation with evidence of cardiotoxicity. Although the optimal method to effectively treat leukemia while preserving cardiac function has not been established, careful attention to this balance is warranted, and this study will provide key data to inform evolving cardioprotective strategies.

## Conclusion

6.

Through rigorous study of cardioprotective interventions in a large, randomized phase 3 study, AAML1831 will elucidate the optimal cardioprotective strategy and identify valuable cardiotoxicity risk predictors to improve both cardiovascular and oncologic outcomes in pediatric AML. Given the innovative strategies employed to optimize the reliability and accuracy of cardiac outcome assessments, AAML1831 will serve as a model for cardiotoxicity assessment in future pediatric oncology trials.

## Data Availability

The original contributions presented in the study are included in the article, and further inquiries can be directed to the corresponding author.
